##### **7.1.3.1. Parasite-dependent immune-mediated myocardial damage:**

During primo-infection, shortly after macrophage invasion, IL-12/TNF- $\alpha$ -stimulated NK cells produce a peak of IFN- $\gamma$  secretion to control parasite replication at the expense of decreasing IL-10 production (Cardillo et al., 1996). IL-12 production further contributes to polarizing the immune response towards a wide diversity of pro- and anti-inflammatory profiles (Hasegawa et al., 2002), which explains, in part, the evasion of the immune response.

Due to the parasite's persistence, the host's fate is toward a low-grade but permanent state of immune system activation. In such a scenario, the T-cell response is essential for maintaining the typically low parasitemia in the chronic phase of the disease. However, CCC has a defective cytotoxic T cell response with the gradual depletion of the CD8+ T cell population (Perez-Anton et al., 2020). Furthermore, the TH1/TH2 balance is essential for progression to CCC. The parasite induces a combined response where the balance between excess proinflammatory (IFN- $\gamma$ , TNF- $\alpha$ , IL-1 $\beta$ ) and anti-inflammatory (IL-4, IL-10) cytokines may be critical in the development of CCC (Acevedo et al., 2018). Special mention deserves the TH17 subset as elevated levels of IL-17A may correlate with milder heart disease (Sousa et al., 2017).

*From the above, IFN- $\gamma$ , IL-1 $\beta$ , IL-4, IL-17A, and IL-10 levels could help predict CD progression and outcome after drug therapy (Llaguno et al., 2019), and the inclusion of anti-inflammatory drugs could favorably incline toward a better immune response profile and improve treatment of CCC.*

#### **7.1.3.2. Microvascular involvement in CD:**

Experimental and clinical evidence exists of coronary microvascular alterations leading to ischemic myocardial damage in *T. cruzi*-infected animals and patients with CCC (Rossi et al., 2010). It has been reported by the authors and others that microvascular alterations related to i) regional perfusion alterations (Lemos de Oliveira et al., 2018), ii) platelet activation (González-Herrera et al., 2017; Pengue et al., 2019), and iii) endothelial dysfunction (Campos-Estrada et al., 2015) in mouse hearts chronically infected with *T. cruzi*, are similar to those observed in ischemic cardiomyopathies (Borges et al., 2018).

#### **7.1.3.3. Alterations of regional perfusion:**

Up to 20% to 30% of patients with CCC complain of chest pain that resembles angina pectoris in location and character, unrelated to exertion, and with healthy subepicardial arteries (Lemos de Oliveira et al., 2018). In addition, there are reversible myocardial perfusion defects, which can be reversed with dipyridamole (Tanaka et al., 2019). These defects can be attributed to inflammation around intramural coronary arteries causing redistribution of coronary flow from ischemic to non-ischemic regions, thus inducing the appearance of the clinical picture consistent with coronary microvascular dysfunction (Bestetti and Restini, 2014). This aspect may be correlated with autonomic denervation (Barizon et al., 2020), even before the appearance of fibrosis.

#### **7.1.3.4. Endothelial dysfunction:**

Impaired perfusion may directly result from microvascular damage secondary to endothelial activation induced by *T. cruzi* infection and subsequent interaction with immune effector cells. Activated endothelial cells (ECs) produce various cytokines, including the vasoconstriction-inducing molecules endothelin-1 and thromboxane A2 (TXA2) (Hernandez et al., 2018). As we previously demonstrated, ECs also increase the production of cell adhesion molecules such as Intercellular Cell Adhesion Molecules type 1 (ICAM-1), Vascular Cell Adhesion Molecules (VCAM), and E-selectin, including a soluble form of cell adhesion molecules (sCAM) found in blood (Campos-Estrada et al., 2015; Gonzalez-Herrera et al., 2017; Molina-Berrios et al., 2013b). We also demonstrated that the induction of adhesion molecules is mediated by the activation of inflammatory signaling cascades (Campos-Estrada et al., 2015), amplifying the initial inflammatory input. In addition, cytokine production from immune and activated EC facilitates the migration of inflammatory cells and monocytes to the subendothelium, where they produce a local inflammatory response, increasing endothelial damage (González-Herrera et al., 2017; Marín-Neto et al., 2013) and the perfusion alterations mentioned above. All these molecules are potential biomarkers for predicting thrombotic or endothelial disorders (Cortes-Serra et al., 2020). In particular, E-selectin may be an excellent candidate, as it is exclusively expressed in vascular ECs (Dzikowska-Diduch et al., 2017).

Therefore, myocardial perfusion disorders, due to endothelial damage and microcirculatory alterations, contribute to the progression of LV segmental dysfunction observed in the chronic phase of CD (Hiss et al., 2009). Any therapeutic approach to improve left ventricular function or prevent these vascular alterations could benefit patients with CD.

*Overall, considering the role of the endothelium in initiating and propagating vascular wall injury in CD, it is necessary to evaluate pharmacological treatments capable of inhibiting EC activation, dysfunction, and vascular damage in patients with chronic CD.*

#### **7.1.4. Treatment of chronic chagasic cardiomyopathy and strategies of improvement:**

In Chile, etiologic treatment of CD is with 5-10 mg/kg/day of nifurtimox (NFX) or 5 mg/kg/day of benznidazole (BZD) for 60 days (MINSAL, 2017). All patients should receive antichagasic treatment without exclusion or delay, except during pregnancy and lactation, although there is recent evidence suggesting that NFX may be safe in these conditions (Moroni et al., 2019). Also, hypersensitivity to trypanocidal drugs excludes its use. Other exclusions are severe renal, hepatic, or cardiac disease, including CCC with structural compromise, alcoholism (Antabuse effect of NFX), and severe megacolon or megaesophagus (MINSAL, 2017).

Treatment of CD is associated with an increased risk of serious adverse events (AEs), with a mean incidence of 16.20% (PAHO, 2018), a situation that may force discontinuation of therapy in up to 48% of patients receiving NFX (Crespillo-Andujar et al., 2018a; Crespillo-Andujar et al., 2018b; Jackson et al., 2020). AEs include weight loss greater than 5-15%, digestive disorders (nausea, vomiting, diarrhea, epigastralgia and dyspepsia, abdominal distension), headaches, irritability, insomnia, mood disorders, memory loss, fever, arthralgias, myalgias, severe or significant skin and mucosal rashes such as Stevens-Johnson syndrome, evidence of thrombocytopenia, pancytopenia or signs of bone marrow depression, elevated transaminases, leukopenia below 2500/mm^3, CNS disorders such as paresis, paralysis or seizures, and behavioral changes, especially in the case of NFX.

Pharmacological treatment during the acute phase, congenital disease, and early indeterminate phase has satisfactory efficacy and is considered curative (Sales Junior et al., 2017). However, it is more difficult to declare a cure for chronic infection because the current evidence for drug efficacy in this phase is weak or controversial, especially when mortality is considered (PAHO, 2018). After five years of follow-up, BZD could not significantly reduce clinical cardiac deterioration in patients with mild heart disease (Morillo et al., 2015). Moreover, long-term follow-up is required to confirm seroreversion, making serology a weak surrogate as a criterion for cure in chronic CD (Sguassero et al., 2018). Novel therapies, such as the antifungal drugs posaconazole or ravuconazole, were not successful (Molina et al., 2014; Molina et al., 2017; Torrico et al., 2018). Thus, rigorous clinical trials have not demonstrated convincing evidence of clinical benefit or eradication of parasitemia in chronic CD.

Therefore, finding innovative approaches to treat this neglected life-threatening tropical disease is paramount. Three considerations support this claim: i) current therapy for CD in the chronic phase is unsuccessful and increases the risk of systemic toxicity, AE, and poor adherence to treatment or noncompliance; ii) none of the many potential trypanocidal compounds listed is superior to NFX or BZD (Ribeiro et al., 2020); and iii) most antiparasitic drugs are considered orphan drugs due to the low return of development costs to the pharmaceutical industry (Varela and Fernandes, 2020). *Therefore, improving the efficacy of current antiparasitic drugs by modifying host factors such as the inflammatory response - mainly by repurposing existing drugs - would make current treatment more effective.*

#### **7.2. Role of statins in the inflammatory process during chronic Chagas disease**

There are molecules involved in the natural resolution of inflammation. These specialized pro-resolution mediators include several lipids that control the magnitude and duration of local inflammation (Serhan and Chiang, 2013). These lipids are derived from essential fatty acids in the

plasma membrane, such as arachidonic acid or docosahexaenoic acid. Interestingly, aspirin and cholesterol-lowering statins, including atorvastatin (ATO), can S-nitrosylate the enzyme cyclooxygenase-2 (COX2) at amino acid 298, which allows it to produce precursors no longer for the synthesis of prostaglandins (which are pro-inflammatory), but epimers that, through the action of 5-lipoxygenase (5-LO), will give rise to more stable molecules, such as 15-epi-lipoxin A4 (LXA4) or aspirin-activated resolvin D1 (AT-RvD1)(Serhan, 2017; Spite and Serhan, 2010).

The responsible investigator and his team conducted several preclinical studies with results suggesting that aspirin and simvastatin decrease cardiac inflammation and endothelial activation in *T. cruzi* chronically infected mice (Lopez-Munoz et al., 2010; Molina-Berrios et al., 2013b; Molina-Berrios et al., 2013c). 15-epi-LXA4 mediates this action (Campos-Estrada et al., 2015; González-Herrera et al., 2017; Molina-Berrios et al., 2013a) in a process that involves a decrease in the activity of the proinflammatory NF-κB pathway (Campos-Estrada et al., 2015). Furthermore, simvastatin improves, independently of 15-epi-LXA4 activity, ventricular function in chronically infected BALB/c mice (Guzmán-Rivera et al., 2020), while ongoing studies show that aspirin/statin-triggered resolvin D1 (AT-RvD1) improves cardiac electrical function, in the absence of trypanocidal treatment.

*It follows that a combination of trypanocidal drugs and those that induce the resolution of the inflammatory process derived from the persistence of the parasite could be an excellent therapeutic strategy to prevent the chronic consequences of CD.*

Although the preclinical evidence suggests that a statin could benefit chronic CD, this matter has not been tested in the clinical setting. There is only one mention of the use of rosuvastatin in the treatment of CD, but the quality of the evidence provided is poor (Marti-Carvajal and Kwong, 2016). Other clinical trials that focused only on symptomatic treatment of heart failure associated with CD have tested amiodarone (Stein et al., 2018), carvedilol (Botoni et al., 2007), and angiotensin-modulating drugs (Souza-Silva et al., 2019). Other drugs studied in small clinical trials are allopurinol, itraconazole, or ketoconazole, with mixed results (Apt et al., 1998; Apt et al., 2013; Brener et al., 1993); unfortunately, more clinical trials with these drugs are lacking. A major obstacle to drug development is the poor translation of in vivo data to human disease. **Thus, our proposal aims to analyze whether a statin improves the efficacy of antichagasic therapy in the context of Chronic Chagas Disease through a double-blind phase II clinical trial and to evaluate the inflammatory parameters associated with the observed improvement.**

There is widespread agreement that adults with chronic indeterminate CD are the population with the most urgent need for developing new treatments due to the increased disease burden for these patients. Thus, improving host factors (e.g., provoked immune reaction) may increase the efficacy of conventional antichagasic therapy, probably by decreasing doses, reducing their duration, or both.

Given the paucity of evidence-based treatments for this disease, this study will provide an opportunity to assess the impact of a novel therapeutic strategy on a combination of promising candidate markers of inflammation, endothelial activity, and cardiac function associated with sustained improvement and correlate the results with parasitological outcomes. *Thus, this trial*

*could be the first step in evaluating a potential therapy proposed to modify the course of chronic indeterminate CD favorably.*

Although our preclinical studies were performed with simvastatin, we propose atorvastatin (ATO) as an experimental statin. As simvastatin is associated with ezetimibe, it will not be considered in this study. ATO's therapeutic and safety profiles are well known, as well as its mechanism of action and pharmacological actions, including its anti-inflammatory properties, which are shared by the other members of the statin class. Due to the low incidence of severe AEs and its efficacy, ATO is one of the most widely used statins. 20-80 mg/day of ATO are used to lower the so-called LDL cholesterol, implicated in the pathogenesis of the atherosclerotic cardiovascular disease. However, a clinical phase II proof-of-concept study is imperative because i) it is a way to translate the results obtained in the animal model, and ii) a minimum effective dose and safety need to be evaluated in the context of the patient undergoing treatment of chronic CD and, most importantly, iii) because statins are not currently approved for the treatment of CD.

Considering i) the high burden of disease; ii) the role of the endothelium and inflammation in the initiation and propagation of vascular wall injury in CD; iii) that current therapy for CD in the chronic phase is unsuccessful and increases the risk of systemic toxicity, AEs, and poor compliance; iv) that improving the efficacy of current antichagasic drugs by modifying host responses would make current treatment more effective; v) that preclinical evidence suggests that statins may have a role in preventing cardiac damage in CD; vi) that statins are safe and with a well-known pharmacological profile; then, a combination of trypanocidal drugs with those that induce resolution of the inflammatory process resulting from parasite persistence could be an effective therapeutic strategy to prevent the chronic consequences of CD. Consequently, it is proposed that the following hypothesis:

**In patients with chronic Chagas disease, statins improve the efficacy of antiparasitic treatment by decreasing inflammation and improving endothelial and cardiac function**

## **8. OBJECTIVE AND GOALS OF THE TRIAL**

### **8.1. Primary Goal:**

To evaluate the use of atorvastatin, in combination with antiparasitic therapy (NFX or BZD), is safe and more effective than antiparasitic therapy alone in preventing the occurrence of cardiac disturbances by reducing overall inflammation and in improving endothelial and cardiac functions.

To assess the primary endpoint, the number of patients with a change in the stage of chronic cardiomyopathy in 12 months from the beginning of antichagasic treatment will be considered.

We will evaluate whether the effect of atorvastatin in combination with antiparasitic treatment (NFX or BZD) is more effective than antiparasitic therapy alone (placebo group) in preventing the appearance of cardiac disorders determined by non-progression from stage A according to the First Latin American Guidelines for the diagnosis and treatment of chagasic cardiomyopathy (Andrade et al, Arq Bras Cardiol 2011;97 Suppl 3:1-48.) To make this assessment, significant changes in i) electrocardiogram (heart rate and QT interval duration, as well as the appearance of electrical conduction disorders, determined by QRS segment duration and morphology), ii) ejection fraction

(assessed by echocardiography), and iii) cardiac silhouette size (chest X-ray) will be taken into account

## 8.2. Secondary goals:

8.2.1. To evaluate the efficacy of the combination of ATO and antichagasic therapy to decrease:

- Inflammation, as measured by plasma levels of the cytokines, TNF- $\alpha$ , IFN- $\gamma$ , IL-10, IL-1B, IL-4, and IL-17A.
- Endothelial activation, as measured by plasma levels of sCAM: sE-selectin, sICAM-1, and sVCAM-1.
- Cardiac damage and function: measured by plasma levels of BNP, cTnT, 12-lead resting ECG (heart rate, QT segment duration, and electrical conduction changes determined by QRS segment duration and morphology), and 2D echocardiogram (ejection fraction).

8.2.2. To determine the safety and tolerability of the combination of ATO with antichagasic therapy, measured by the incidence of AEs (e.g., rhabdomyolysis) and treatment discontinuation.

8.2.3. To evaluate the treatment response to the combination of ATO with antichagasic therapy, as measured by quantitative PCR and serology, over a 10-month follow-up period.

8.2.4. To determine the degree of therapy adherence by measuring drug accountability throughout the study.

## 9. Study design:

### 9.1. Outcomes:

As in any clinical trial, the results should be clearly defined beforehand. Thus, the **primary outcome** of this study at 12 months is the change in cardiac function in patients with chronic CAD. To this end, the number or proportion of patients presenting a change in the phase of chronic cardiomyopathy will be assessed. This phase change is determined by non-progression or reversion from or to phase A, according to the I Latin American Guidelines for the diagnosis and treatment of chagasic cardiomyopathy (Andrade et al., 2011), considering the consistent findings of structural alteration evidenced by changes in clinical, electrocardiographic, echocardiographic parameters and, additionally, of plasma levels of the cardiac function biomarkers BNP, cTnT.

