## 9.2. Statistical analysis: see section 11.

Clinical events related to CD occur at a low incidence in patients with the indeterminate CD due to the pathogenesis and hysteresis of the disease, parasite characteristics, and host response times; therefore, extensive clinical trials would be needed to assess changes in incidence. In addition, serologic and clinical endpoints of cure would require several years to decades in chronic CD (Bern, 2015). Consequently, the criterion of cure as a primary outcome, determined by seroreversion, is not considered in this proposal.

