## 10. SELECTION AND WITHDRAWAL OF SUBJECTS

### 10.1. Inclusion criteria:

Subjects eligible to be enrolled in this trial must be adults older than 18 years and younger than 50 years, weighing more than 40 kg, with a conventional confirmatory serology for *T. cruzi* infection from the Instituto de Salud Pública de Chile (ISPCH). A positive qPCR will be selected to participate in this trial. Only patients with a new diagnosis of Chagas disease in the chronic indeterminate phase will be included. In addition, they must have normal values in laboratory tests for the following parameters: total white blood cell count, platelet count, creatine kinase (CK), alanine aminotransferase (ALT), aspartate aminotransferase (AST), total bilirubin or creatinine, or a gamma-glutamyl transferase (GGT)  $\leq 2$  times the upper limit of normal (X ULN); Women of reproductive age must have a negative serum pregnancy test, must not be breastfeeding, and must consistently use a highly effective method of contraception throughout the treatment phase.

Subjects must also meet all the following criteria: the ability to comply with all tests and follow-up visits specified in the protocol and have a permanent address; sign the written informed consent form.

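### Primary outcome: sections 8.1 and 9.1 count a change of stage, but 9.1 defines that change as non-progression or reversion, so the counted event and its status as success or failure conflict

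*Protocol*

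**What the plan says.** Section 9.1 says the primary outcome "of this study at 12 months is the change in cardiac function". To measure it, "the number or proportion of patients presenting a change in the phase of chronic cardiomyopathy will be assessed". The next sentence defines the event: "This phase change is determined by non-progression or reversion from or to phase A", with phases taken from the guideline classification in Chart 1.

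Section 8.1 gives the same count for the primary endpoint, "the number of patients with a change in the stage of chronic cardiomyopathy in 12 months", timed from the start of antichagasic treatment. It then describes the aim as "preventing the appearance of cardiac disorders determined by non-progression from stage A".

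Two other statements bear on this:
- Section 10.1, on entry: "Only patients with a new diagnosis of Chagas disease in the chronic indeterminate phase will be included". Chart 1 puts the indeterminate form under A.
- Section 9.2, on frequency: "Clinical events related to CD occur at a low incidence in patients with the indeterminate CD". It gives no rate.

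The analysis sections use other variables. Section 12.1 sizes the trial on the proportion of patients whose ECG, echocardiogram, BNP and cTnT improve by end of treatment, 0.40 against 0.20. Section 12.4, and the efficacy paragraph of the Summary, analyse the primary outcome with a one-sided Fisher's exact test of the proportion with a significant biomarker decrease.

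**The concern.** The event to be counted is a change. The definition attached to it names two states, one of which, non-progression, is the lack of a change. In a population that enters in phase A, the count and the definition therefore select opposite patients: the first selects those who get worse, the second mainly those who stay where they are.

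This is the primary endpoint, and the protocol fixes it in conflicting terms rather than leaving it open. An analysis plan would have to override one of two adjacent sentences. The direction matters in particular because 12.4 announces a one-sided test for the primary outcome, and such a test needs to know whether a higher count is the hoped-for result.

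**Working it through.** **1. The plan's own figure.** Section 12.1 gives 75 evaluable patients per group for 0.40 against 0.20, two-sided 5%, 90% power. The usual formula is n = [z(0.975)·√(2·p̄·q̄) + z(0.90)·√(p1·q1 + p2·q2)]² / (p1 − p2)². With p̄ = 0.30 this is [1.960·√0.42 + 1.282·√0.40]² / 0.04 = 2.081² / 0.04 = 108.2, so 109 per group (119 with continuity correction). The 75 does not reproduce. The dropout step does: 75 / 0.75 = 100. The sample-size discrepancy is a separate matter, and the present point does not depend on it.

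**2. Count and definition side by side.** Entry in phase A (10.1, Chart 1). The third column uses the natural reading of 9.1: non-progression from A, or reversion to A.

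| Patient's course | Has a change of phase (count in 8.1 and 9.1)? | Meets the 9.1 definition? | Value implied by 8.1 |
|---|---|---|---|
| A throughout | No | Yes, non-progression | Good |
| A to B1 or higher, still so at day 360 | Yes | No | Bad |
| A to B1, back to A by day 360 | Yes during follow-up; no if screening is compared with day 360 | Yes, reversion | Not stated |

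The first two rows cover nearly everyone, and in both the count and the definition disagree. The third row has little room in the schedule in 9.6. The echocardiogram is done only at screening and day 360. The chest X-ray adds one intermediate look, at day 120. The ECG adds days 60 and 120, and days 180 and 240 only after an earlier abnormality.

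**3. Does section 12.1 settle the event?** Suppose the 0.20 for placebo were the rate of non-progression. Then 1 − 0.20 = 80% of placebo patients would leave phase A, against the low incidence described in 9.2. If it were reversion to A, nobody in A at entry could have the event without first progressing. If it were progression, atorvastatin at 0.40 would be doing worse than placebo. The 12.1 rates therefore fit none of the stage-based readings, and the biomarker variable in 12.4 is different again.

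**4. Do the two sides of one binary outcome give different answers?** Assume 2 of 100 progress on atorvastatin and 5 of 100 on placebo (the protocol gives no rate).
- Progression: 2% against 5%, difference −3 points, odds ratio (2/98)/(5/95) = 0.39.
- Non-progression: 98% against 95%, difference +3 points, odds ratio (98/2)/(95/5) = 2.58 = 1/0.39.

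These are complements, with the same two-sided p-value. Given the direction in 8.1, the conclusion is the same.

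**5. What a one-sided test does with each coding.** Assumptions: 75 per arm, one-sided 5% Fisher test that more events on atorvastatin is the favourable direction, and placebo progression halved by atorvastatin.

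| Assumed placebo progression | Power, non-progression as success | Power, change as success |
|---|---|---|
| 2% | 0.8% | 0.02% |
| 5% | 8.1% | 0.12% |
| 10% | 22.8% | 0.10% |
| 20% | 44.5% | 0.02% |

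The right-hand column is what follows if the word change is taken as the favourable event. A one-sided test then cannot detect a protective effect. Even the correct coding has low power across this range.

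**The case against.** The clinical intent is not in doubt. The aim in 8.1 is prevention, tied to staying in stage A, and the hypothesis in the Summary is that cardiac function improves. The 9.1 phrase reads naturally as non-progression from A, or reversion to A, which makes both components favourable and leaves an A-to-B1 move outside the definition. The clumsiness may come from translation. All of this stands.

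A reader might infer more than the documents support:
- **That the favourable direction is undefined.** It is not: 8.1 makes non-progression from A the good result.
- **That two analysts could report opposite results from the same data.** Step 4 shows that progression and non-progression are complements. An opposite conclusion needs an analyst to score progression as success, against 8.1.
- **That patients who stay and patients who leave could all be counted, giving 100% in each arm.** This takes the phrase at its most literal and merges it with the sentence it is meant to define. Nobody would plausibly run that analysis.

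One could also argue that reversion is available to some patients, because 10.2 excludes only stage II or higher on a different staging scale. But 10.1 restricts entry to the indeterminate form, and 9.7 excludes clinically significant ECG abnormalities.

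What the objection does not remove is that non-progression is labelled a change, that 8.1 and 9.1 both count changes, and that no section says whether a higher count is better.

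**Conclusion.** The point holds as a contradiction in the definition of the primary event. The direction of benefit can be inferred. The counted event, and whether it is a success or a failure, cannot be read consistently from 8.1 and 9.1, and 12.1 and 12.4 do not resolve it. This is wrong as written, not detail left for an analysis plan, and it matters because the primary outcome is assigned a one-sided test.

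The contradiction rests on wording alone and needs no assumed rate. The power figures in step 5 are illustrations under assumed progression of 2% to 20% and a halving by atorvastatin. They show why the direction must be fixed and that a stage-based event may be badly underpowered. They do not estimate this trial's actual power.

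**What to change.** State one event in 8.1 and 9.1, with its direction. For example: phase A at screening and B1 or higher of Chart 1 by day 360, counted as a failure, fewer events favouring atorvastatin. Its complement, non-progression counted as a success, serves equally well. Remove the 9.1 phrase on non-progression or reversion from or to phase A, replace the count of changes in 8.1, and report any reversion descriptively.

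Use the same event and direction in 12.1 and 12.4 and in the matching efficacy paragraph of the Summary. Editing only 8.1 and 9.1 would leave the trial sized on patients who improve and tested on biomarker decrease.

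The cost is a protocol amendment. No new visits or examinations are needed, since ECG, chest X-ray and echocardiogram are already scheduled at screening and day 360. The real price is the power statement. The 0.40 against 0.20 assumption and the 90% do not transfer to an event that 9.2 suggests is rare. The amendment should give an assumed progression rate with its basis and restate the power that 100 recruited per group provides, even if it is low.
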